##### Rapid Sound Sequences Task

The Rapid Sound Sequences task consists of auditory stimuli 6 seconds-long sequences of subsequent tone pips (50 ms duration), drawn from a pregenerated pool of 20 fixed frequencies. Each sequence is followed by a 2-second interstimulus interval. The tone-pip sequences are arranged according to varying patterns and are randomly generated for each participant and on each trial. Conditions vary by levels of auditory regularity and irregularity with 2 control and 3 transition conditions. Previous research showed that transitions from regularity to irregularity evoked pupillary responses [24].

Control condition regular 10 (REG10): randomly selecting 10 frequencies from the pool, arranging them in a fixed sequence pattern, and iterating the sequence to create a regular pattern.Control condition random 20 (RAND20): randomly selecting 20 frequencies with replacement from the pool and playing these fully randomized.Transition condition REG10-RAND20: the first 3 seconds are presented as REG10, followed by a transition to RAND20 for 3 seconds.Transition condition RAND20-REG10: the first 3 seconds are presented as RAND20, followed by a transition to REG10 for 3 seconds.The transition condition RAND20-REG1: the sequence starts as RAND20 for 3 seconds and transitions into REG1, a single tone pip selected from the pool and iterated for the final 3 seconds.

Each control condition will be presented 5 times, and each transition condition 10 times, in randomized order. Attention will be directed to the screen center by a fixcross or a video and controlled for by gaze-contingent trial presentation. Deviant gazes will evoke an attention-grabbing stimulus to redirect attention. A silent cartoon will be presented during the interstimulus interval.

##### Visual Oddball Task

The visual oddball task consists of 72 trials displaying frequent (standard size: 2.9° visual degrees; 80%) and infrequent (oddball size: 4.6° visual degrees; 20%) blue circles. Each stimulus is displayed for a 150-millisecond duration and is preceded by a 1.5-second interstimulus interval. Attention is maintained using gaze-contingent trial presentation.

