##### Auditory Oddball Task

A passive auditory oddball task that is feasible in preschoolers (see 1.3, Figure 2) will be applied as a reference measure [90]. The auditory oddball task consists of a series (k=100) of frequent (“standard,” 80%) or infrequent (“oddball,” 20%) pure tones. Pure tones will have a short duration (50 ms) and will be presented with an interstimulus interval of a random duration between 1.8 and 2 seconds, while the pitch of the pure tones (500 or 750 Hz) will be counterbalanced between participants. Attention will be directed to the screen center by a continuous cartoon video without sound and controlled for by gaze-contingent trial presentation. Deviant gazes will evoke an attention-grabbing stimulus to redirect attention.

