### Neurophysiological Measures

BPS and SEPR are assessed for each trial in each task. BPS is defined as the pupil size prior to stimulus onset, while SEPR represents a pupil size change in response to stimuli. BPS and SEPR will be evaluated in the auditory oddball task in response to standard trials as neurophysiological habituation [99] and to oddball trials as sensory selectivity [33].

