### Expected Outcome and Study Hypotheses

A successful task manipulation will be indicated by a higher SEPR in oddball versus standard trials (ie, sensory selectivity) and declining BPS across standard trials (ie, habituation). We expect convergent validity with moderate-to-high correlations between the auditory oddball SEPR and the pupillometric measures in the validation tasks (including SEPR to a change from regularity to irregularity, SEPR to visual oddball stimuli, and SEPR before target detection). We expect convergent validity in the hetero-method analyses, whereas we expect divergent validity with cognitive and language development.

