##### Neurophysiological Measures

At each time point, the validated pupillometric battery, as described in Objective 1, will be used to assess BPS and SEPR across multiple tasks.

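### Visual oddball task: the oddball is always the larger circle, so rarity and size cannot be separated at group level, and size or light reactivity can enter the visual SEPR

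*Protocol article*

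**What the plan says.** All references are to the protocol article.

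- **Visual Oddball Task.** There are 72 trials in all, and the stimuli are specified as "displaying frequent (standard size: 2.9° visual degrees; 80%) and infrequent (oddball size: 4.6° visual degrees; 20%) blue circles". On timing, the section adds: "Each stimulus is displayed for a 150-millisecond duration and is preceded by a 1.5-second interstimulus interval". The section gives one assignment of size to role. It mentions no swapping of sizes between children and no size-matched control.
- **Auditory Oddball Task.** In the corresponding auditory task, "the pitch of the pure tones (500 or 750 Hz) will be counterbalanced between participants".
- **Neurophysiological Measures (Work Package 1).** "SEPR represents a pupil size change in response to stimuli". The definition does not separate a light or size component. The section then names the auditory oddball as the task in which standard trials stand for habituation and oddball trials for sensory selectivity.
- **Statistical Analysis Plan and Expected Outcome (Work Package 1).** Visual oddball SEPR is one of the measures expected to correlate with auditory oddball SEPR. The pattern of intercorrelations shapes the concise battery.
- **Table 1 and Task 3.1.** Table 1 lists the visual oddball as a measure of LC-NE activity from objective 1.1 through 3.2. In Task 3.1, at each time point, "the validated pupillometric battery, as described in Objective 1, will be used to assess BPS and SEPR across multiple tasks".

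**The concern.** An oddball contrast should isolate the effect of a stimulus being rare. That requires rare and frequent stimuli to be physically equivalent, or the physical difference to be balanced across children. Here every rare circle is the large one and every frequent circle the small one.

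The problem is sharper than in most oddball designs because the outcome is pupil size. A larger disc changes the light reaching the eye more than a smaller one, unless it is isoluminant with its background. Baseline correction does not help, since the response to size or light is itself evoked by the stimulus.

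Two uses of the visual SEPR are exposed. The first is any group-level statement that children respond to visual deviance. The second is the between-child use: visual SEPR as a convergent criterion for the auditory SEPR, and later as an LC-NE indicator beside it. If children differ in how strongly their pupils react to size or light, that difference is read as LC-NE functioning.

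**Working it through.** The article gives no numerical claim for the visual task, so there is no figure to reproduce. The stated power of Work Package 1 concerns the auditory oddball.

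**Inputs.** Circle sizes 2.9° and 4.6°, 72 trials, 80%/20% split (Visual Oddball Task). Disc and background luminance are not given. The ratio k in step 3 is an assumption, shown over a range.

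**1. Physical difference.** Diameter ratio: 4.6/2.9 = 1.59. Area ratio: (4.6/2.9)² = 2.52. Areas: π × 1.45² = 6.6 and π × 2.3² = 16.6 square degrees. Each child sees about 0.20 × 72 = 14.4, so roughly 14 oddballs, all of the larger size.

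**2. Group contrast.** Let mean SEPR = b0 + bD × (rare) + bS × (large), assuming the two effects add.

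- As described, standards are (rare, large) = (0, 0) and oddballs (1, 1). The two columns are identical, the design matrix has rank 2 for 3 parameters, and the contrast equals bD + bS. More children or trials do not change this.
- With sizes swapped for half the children, the contrast is bD + bS in one half and bD − bS in the other. Their average is bD and half their difference is bS. The rank is 3 of 3.

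**3. Between-child correlation.** Write child i's visual contrast score as V(i) + L(i), with V the deviance response and L the size or light response. Suppose L is independent of V and of the auditory SEPR, and let k = Var(L)/Var(V). Then

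r(observed) = r(true) / √(1 + k).

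| True r | k = 0 | k = 0.25 | k = 0.5 | k = 1 | k = 2 |
|---|---|---|---|---|---|
| 0.3 | 0.30 | 0.27 | 0.24 | 0.21 | 0.17 |
| 0.5 | 0.50 | 0.45 | 0.41 | 0.35 | 0.29 |

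If L is the same for all children, k = 0 and the correlation is untouched. Only individual differences in L matter.

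**4. What counterbalancing does to that correlation.** The score becomes V(i) + L(i) in one half and V(i) − L(i) in the other. An assignment covariate removes the mean shift, but the remaining variance is still Var(V) + Var(L). Under the independence assumption the attenuation in step 3 is therefore unchanged. If L is instead related to the auditory SEPR A, the covariance with the visual score is Cov(A,V) + Cov(A,L) in one half and Cov(A,V) − Cov(A,L) in the other. In equal halves the second term cancels on average. Counterbalancing thus removes a one-directional distortion of the contrast score, but not added noise.

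**The case against.** Several points on the other side are sound and limit the reach of this one.

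- **Manipulation check.** A reader might infer that the check in Work Package 1, "A successful task manipulation will be indicated by a higher SEPR in oddball versus standard trials (ie, sensory selectivity", could falsely pass or fail in the visual task. The text does not support this. The sentence names no task, but its two labels, sensory selectivity and habituation, are tied to the auditory oddball under Neurophysiological Measures, and there pitch is counterbalanced. The visual SEPR is then listed separately among the validation measures.
- **Choice of tasks.** A reader might also infer that the visual task will be kept or dropped on its oddball-minus-standard difference. The analysis plan shortens the battery on intercorrelations, which a response common to all children leaves unchanged.
- **Unknown size.** The factor of 2.5 is geometry, not a pupil effect. Luminance matching is a detail that an article may leave to fuller documents, so its absence is not itself a fault. The task code is in a repository that is not shown and might counterbalance.
- **Individual differences.** Showing every child the same stimuli is a defensible choice for a predictor that is compared between children, and step 4 shows that swapping sizes does not remove independent child-level variance.
- **Validation.** By February 2026, 82 of the planned 90 children had been assessed with the present stimuli. Reversing the sizes gives half the cohort a version that Work Package 1 did not test.

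What remains is that the fixed mapping is stated outright, acts on the outcome itself, and is avoided in the parallel auditory task. If the code already counterbalances, the article's description needs correcting.

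**Conclusion.** The point holds in a limited form. As described, rarity and size coincide completely in the visual oddball task, so its group-level SEPR contrast is not evidence of deviance detection alone. The visual SEPR may also carry between-child differences in size or light reactivity into the convergent-validity analysis and the later LC-NE measures.

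The stimulus difference is 2.5-fold in area and applies to every visual oddball trial. The resulting pupil effect has unknown size and sign: a disc brighter than its background would push the oddball response toward constriction, a darker one toward dilation. If the disc were isoluminant, the light component would shrink, but the size difference would still coincide with rarity. The correlations in step 3 are illustrations that rest on an assumed k and on independence.

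It would go too far to infer that the visual SEPR is useless or that the validation fails. It is one of three comparison tasks, and the auditory oddball, which is the required reference task, is unaffected. This is a cheap improvement worth making before the longitudinal study starts.

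**What to change.** **Longitudinal battery (scheduled for April 2026).** Counterbalance between children which size is standard and which is oddball. Keep each child's assignment fixed over T1 to T3, and include assignment as a covariate in models that use the visual task. State plainly that this separates deviance from size at group level and does not remove child-level size or light variance.

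**Work Package 1.** Do not interpret a visual oddball-versus-standard SEPR difference as pure sensory selectivity. When the visual SEPR correlation is used to shape the battery, treat it as possibly including size or light reactivity.

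**Cost.** A change to the task script and one covariate, with no added visits, staff or testing time. The real price is comparability: half the children will see a size assignment that the Work Package 1 sample did not see. Changing after T1 has begun would also disturb comparison across waves, so the decision belongs before the start. Making the discs isoluminant is a weaker alternative, because size would still coincide with rarity and the stimuli might change for every child.

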##### Audio-Cued Visual Search Task

Each trial presents a visual search display consisting of 4 colored circles (red, yellow, or green) arranged in an imaginary circle around the center of the screen. One circle (target circle) has a deviant color from the 3 distractors, and its position changes randomly across the 30 trials. The visual search phase has a duration of 1.5 seconds. An auditory alerting cue, a simple brief beep, is presented in 50% of the trials. The cue duration varies randomly between 200 and 300 milliseconds and is presented with a random delay of 0‐100 milliseconds within a 400-millisecond interval prior to the visual search onset. Each trial starts with a 1.5-second interstimulus interval with a fixation cross in the center of the screen. Attention is maintained using gaze-contingent trial presentation.

### Neurophysiological Measures

BPS and SEPR are assessed for each trial in each task. BPS is defined as the pupil size prior to stimulus onset, while SEPR represents a pupil size change in response to stimuli. BPS and SEPR will be evaluated in the auditory oddball task in response to standard trials as neurophysiological habituation [99] and to oddball trials as sensory selectivity [33].

### Cognitive Measure

To assess the verbal and cognitive abilities, we will conduct 2 subtests from the Wechsler Preschool and Primary Scale of Intelligence (WPPSI) [93].

### Statistical Analysis Plan

We will validate the pupillometric indices by a multitrait-multimethod design. In a homo-method analysis, the BPS and SEPR during the auditory oddball task (Figure 5A) will be compared to BPS and SEPR in tasks of LC-NE functioning with irregularity in rapid sound sequences [24] (Figure 5B), a visual oddball task [91] (Figure 5C), and an audio-cued visual search [92] (Figure 5D).

In a hetero-method analysis, the BPS and SEPR during the auditory oddball task will be compared to event-related potentials (ERPs) in concurrent EEG. We investigate oddball ERPs that are likely associated with LC-NE activity (P300, MMN) [27,100]. Finally, the pupillometric measures will be compared to divergent measures of cognitive and language ability as assessed by WPPSI-IV [93]. Patterns of high intercorrelations will be used to create a concise pupillometric battery of LC-NE functioning (~15 min). BPS and SEPR are reliably assessed in few oddball trials (k=20).

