**Methods:**

LOCUS-MENTAL includes 4 work packages. The centerpiece is an accelerated longitudinal study, in which a cohort of 300 preschool-aged children (aged 4‐6 years) will be recruited and followed up across 3 assessment waves, each one year apart. This will characterize developmental trajectories from 4 to 8 years of age. The primary outcome is the prediction of transdiagnostic psychopathology by pupillometry-derived LC-NE functioning. Transdiagnostic psychopathology is assessed by the Child Behavior Checklist (CBCL), while LC-NE functioning is assessed with pupillometry that includes core metrics of baseline pupil size (BPS) and stimulus-evoked pupillary response (SEPR). Cross-lagged panel models will be applied to the longitudinal data for quantifying causal effects between LC-NE functioning, childhood adversity, and psychopathology. Normative modeling and classification approaches will estimate an individual risk prediction based on pupillometric metrics of LC-NE functioning. The pupillometric battery has 4 passive auditory and visual paradigms. This battery will be validated with a multitrait-multimethod design that combines pupillometry with neurophysiological measures in electroencephalography, behavioral and cognitive measures, and neurocognitive paradigms. The study was approved by the Ethics Committee of the Faculty of Medicine at Goethe University Hospital (2024‐2160). Written informed consent will be obtained from caregivers and verbal assent by the children.

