**Figure 3. F3:**
[figure not shown]
Work program of LOCUS-MENTAL with time flow, required personnel, and the associated tasks.

#### Objective 1

This study aims to validate a concise test battery assessing LC-NE system functioning in preschool children using pupillometric measures during passive tasks. The test battery will be evaluated for convergent and discriminant validity.

#### Objective 2

This study aims to associate LC-NE functioning with correlates of psychopathology in a cross-sectional study. Task 2.1 will determine whether LC-NE functioning profiles serve as markers of dispositional risks and differentiate between irritability and behavioral inhibition. Task 2.2 will examine whether LC-NE functioning further mediates the association between childhood adversity and transdiagnostic psychopathology.

#### Objective 3

This study aims to evaluate the prospective effect of LC-NE functioning in a developmental model of vulnerability and stress. Task 3.1 will investigate whether pupillometric measures of LC-NE functioning in preschool age predict risk for psychopathology at school age. Task 3.2 will assess LC-NE functioning as a mediator between early stress responses and later psychopathology.

#### Objective 4

This study aims to develop an objective tool of risk prediction in the preschool ages based on the pupillometric measures of LC-NE functioning. LC-NE function profiles in preschoolers define a normative development space, where individual deviations indicate quantitative risks for MHD.

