#### Experimental Design

This task uses a multitrait, multimethod design combining pupillometry, EEG, and behavioral assessments to validate the pupillometry battery.

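### Work package 1's only labelled discriminant comparison (two WPPSI subtests) differs in both trait and method, so it cannot detect shared pupil variance or data-quality variance unrelated to ability

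*Protocol article*

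**What the plan says.** Objective 1 states: "The test battery will be evaluated for convergent and discriminant validity". The Statistical Analysis Plan of work package 1 opens: "We will validate the pupillometric indices by a multitrait-multimethod design". It then names three sets of comparisons.

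- **Pupil against pupil.** BPS and SEPR of the auditory oddball task "will be compared to BPS and SEPR in tasks of LC-NE functioning with irregularity in rapid sound sequences", and in the visual oddball and the audio-cued visual search.
- **Pupil against EEG.** "We investigate oddball ERPs that are likely associated with LC-NE activity (P300, MMN").
- **Pupil against ability.** "the pupillometric measures will be compared to divergent measures of cognitive and language ability as assessed by WPPSI-IV". The Cognitive Measure section limits this to two subtests.

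The Expected Outcome section treats the first two sets as convergent and adds "whereas we expect divergent validity with cognitive and language development". No threshold is given for any of them.

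On what is collected, the abstract says: "This battery will be validated with a multitrait-multimethod design that combines pupillometry with neurophysiological measures in electroencephalography, behavioral and cognitive measures, and neurocognitive paradigms". The Experimental Design section of work package 1 says: "This task uses a multitrait, multimethod design combining pupillometry, EEG, and behavioral assessments to validate the pupillometry battery". In Table 1, the only entries that start at Objective 1.1 are demographics, the four pupil tasks, the two WPPSI subtests and EEG during the pupil tasks. The temperament and psychopathology questionnaires, the Go/NoGo task and the neurocognitive paradigms start at 2.1.

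**The concern.** A multitrait-multimethod matrix shows method variance through its same-method, different-trait cell. If two supposedly different traits measured by one instrument correlate as strongly as one trait measured twice, the instrument drives the correlations. Work package 1 does not name that cell as discriminant evidence. The cell it does name, different trait by different method, is the easiest to satisfy.

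This matters because the concise battery is to be built from patterns of high intercorrelation, and variance common to all pupil recordings raises those too. The Discussion calls the validation phase a prerequisite for sensitivity and specificity, and Tasks 2.1, 2.2 and 3.1 all use the validated battery. A discriminant result based on the WPPSI alone could be read as stronger support than it is.

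**Working it through.** **1. The plan's own figure.** The only work package 1 power figure is .82 (n=90, b=0.3, oddball stimulus effect). Treating 0.3 as a standardised correlation and assuming two-sided alpha .05 (none is stated), Fisher's z gives atanh(.3)·√87 − 1.96 = .3095·9.327 − 1.96 = .927, and Φ(.927) = .82. The figure is plausible and not in dispute. It says nothing about the discriminant check.

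**2. The named comparisons placed in the matrix.**

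| | Same method (pupil) | Different method |
|---|---|---|
| Same trait (LC-NE) | three further pupil tasks | P300, MMN |
| Different trait | none named | two WPPSI subtests |

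BPS and SEPR are recorded on every trial, and the Introduction treats them as separate tonic and phasic indices. Material for the empty cell therefore exists.

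**3. What the WPPSI comparison can separate.** No criterion is stated, so I take non-significance of both correlations as an illustration. At n=90 the critical value is |r| = 1.987/√(88 + 1.987²) = .207. The simulation used 20,000 runs and independent LC-NE, pupil-method and ability factors. Assumed loadings were .8 for the pupil index on its source, .6 for the ERP on LC-NE and .8 for each subtest on ability. The mixed index loads .57 on LC-NE and .57 on pupil method.

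| Index | Both WPPSI correlations n.s. | Mean r between pupil tasks | ERP correlation significant and positive |
|---|---|---|---|
| LC-NE only | 91.2% | .64 | 99.8% |
| Pupil method only | 91.3% | .64 | 2.4% |
| Mixed | 91.2% | .65 | 91.7% |
| Noise | 91.3% | .00 | 2.6% |

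At n=72 (80% of 90), the method-only index passes the WPPSI check in 91.4% of runs. With |r|<.3 as the criterion, every row is about 99% at n=90. The rates depend on the assumptions. Their equality needs only that each index is unrelated to ability.

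**4. What a within-pupil contrast could show.** Compare r12 (SEPR with SEPR of another task) with r13 (SEPR with BPS) using Steiger's statistic for dependent correlations: Z = (atanh r12 − atanh r13)·√(n−3)/√(2−2s), where s is the covariance term from the pooled correlation and r23. The protocol gives none of these correlations, so all are assumed. The test is one-sided at 5%, n=90, with r23 = .2 in size.

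- .5 vs .2: s = .139, Z = .3466·9.327/1.312 = 2.46, power Φ(2.46 − 1.645) = .79 (.71 at n=72).
- .5 vs .3: Z = 1.69, power .52.
- .4 vs .2: Z = 1.58, power .48.
- .5 vs −.4, compared in absolute value: Z = .87, power .22.

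A formal gate would thus be underpowered in plausible cases. Under the absolute-value form it would also tend to fail an index with a strong negative tonic-phasic relation.

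**The case against.** **Safeguards already exist.** The EEG comparison separates a pure LC-NE index from a pupil index with no LC-NE content (99.8% against 2.4%), and the oddball-versus-standard contrast checks the manipulation. This stands. A reader might infer that a pupil index with no LC-NE content would pass all of work package 1, and the documents do not support that. Still, neither safeguard is discriminant evidence, and the mixed index passes the EEG comparison in 91.7% of runs, so heavy method variance can go unnoticed.

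**The WPPSI check is not empty.** The protocol links pupil dilation to cognitive load and LC-NE to attention and memory, and Task 2.1 lists IQ as a potential covariate. If the true correlation with a subtest were .3, one sample correlation would stay below .3 only about half the time. The check can fail for ability-related variance, so the limitation is confined to variance unrelated to ability.

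**The article may simply be condensed.** Its wording allows BPS-SEPR cross-correlations, and a fuller analysis plan may specify them. This stands in part: it cannot be said that they will go unused, only that the article names the WPPSI alone as divergent.

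**BPS is an imperfect contrast.** The protocol treats it as an LC-NE index. The Introduction's section on acute stress responses says raised tonic activity attenuates phasic activity, while Task 2.1 expects both to rise with behavioral inhibition. This stands, and it rules out an absolute-value pass/fail rule. It is also tempting to think that SEPR against BPS would establish LC-NE specificity. It would not, because a general evoked pupil response with no LC-NE content could also agree across tasks and differ from baseline size.

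**Conclusion.** The point holds for the discriminant evidence only. As described, that evidence lies in the different-trait, different-method cell, where a true LC-NE index and any pupil index unrelated to ability do equally well (about 91% in the illustration). The equality rests on zero correlation with ability. The rates also rest on assumed loadings and an assumed criterion.

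A reader might further infer that the discriminant result formally releases the battery to the 300-child cohort. No section states such a gate; the article says only that battery content follows high intercorrelations and that later tasks use the validated battery.

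Separately, the abstract's inclusion of behavioral measures and neurocognitive paradigms in the validation, and the reference to behavioral assessments in the work package 1 design, do not match Table 1's start points. This is a small inconsistency. Taken together, the point is a worthwhile and inexpensive improvement and does not invalidate the phase.

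**What to change.** 1. Keep the WPPSI comparison. Add to the discriminant evidence, from data already recorded, the signed SEPR-BPS correlations within and across tasks, and the correlations of SEPR and BPS with each child's rate of lost or off-screen gaze. The plan already applies gaze-contingent presentation and per-task validity rates.
2. Report each of these correlations beside the cross-task SEPR-SEPR correlations, with the difference between dependent correlations and its confidence interval. Do not make it a pass/fail gate, given the possible negative tonic-phasic relation and power near .5 in two of the assumed scenarios.
3. State that these contrasts separate the evoked response from baseline size and data quality, while LC-NE specificity still rests on the EEG comparison.
4. Reconcile the abstract and the Experimental Design section of work package 1 with Table 1.

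The cost is a few extra correlations in the analysis planned for March 2026, with no new data. The downside is that the discriminant evidence may look less favourable.
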